## Methods

### Study design

FINGER-NL is a multi-center, randomized, controlled, multidomain lifestyle intervention trial among 1,210 older adults at risk for cognitive decline, with a duration of 24 months. Block-randomization stratified by study site (block sizes of preferably 20–24 participants) was used to centrally allocate eligible participants in a 1:1 ratio to a personalized multidomain lifestyle intervention (HI-group) versus online access to general lifestyle-related health information (LI-group). The multidomain intervention comprises a combination of 7 lifestyle components (physical activity, cognitive training, cardiovascular risk factor management, nutritional counseling, sleep counseling, stress management, social activities) and a nutritional product (Souvenaid, 125 mL). The study is conducted in five study centers across The Netherlands (Amsterdam, Groningen, Maastricht, Nijmegen, Wageningen). Outcome measurements are conducted at baseline, 12 months (Follow-up 1) and 24 months (Follow-up 2) after randomization. A flow-chart of the study design is shown in Fig. 1. FINGER-NL is part of the ‘Maintaining Optimal Cognitive Function In Ageing’ (MOCIA) research program (https://mocia.nl/scientific/).

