### Randomization and blinding

Participants were randomized after providing written informed consent and after completing the baseline visit. Participants were allocated randomly into either the HI-group or the LI-group using a computer random number generator with randomly varied permuted blocks of 4 to 6 and an equal 1:1 allocation ratio, stratified by study site. Randomization took preferably place per 24 participants per site simultaneously, resulting in balanced HI-groups and LI-groups of 12 participants each and equal starting point of the intervention. To promote blinding and adherence, and inspired by U.S. POINTER [26], we deliberately avoid the label ‘control group’, but rather designate both groups as receiving some form of lifestyle intervention, differing however in structure and intensity. Personnel collecting the primary outcome measures (cognition) and researchers conducting the statistical analyses are blinded to group allocation.

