### Primary outcome

The primary outcome is the 2-year change from baseline in a global cognitive composite score derived from subtest scores from the neuropsychological test battery (NTB). The NTB includes (i) 15-Word Verbal Learning Test delayed recall (episodic memory) [28], (ii) Digit Symbol Substitution Test 90 seconds (processing speed) [29], (iii) Wechsler Adult Intelligence Scale digit span backwards [30], and (iv) semantic fluency (animals; both attention and executive functions) [31, 32]. The choice for this subset was based on consultations with neuropsychologists to cover the cognitive domains attention and executive functioning, processing speed and memory, their sensitivity to early cognitive changes in older individuals, administration time, and suitability for harmonization with other large multidomain intervention studies. The raw scores of individual tests will be transformed into standardized z-scores using the cohort-wide means and standard deviations (SD) at baseline (with higher scores suggesting better performance). The NTB total score is obtained by averaging the z-scores of the four individual tests and re-standardization. The minimum number of necessary individual tests was set to 3 out of 4 for calculating the NTB total score.

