### Sample size

Sample size calculation was based on the primary outcome (NTB total score). In the original FINGER trial [8], an effect size of 0.127 (Cohen’s d) was reported for the 2-year change from baseline on the NTB total score following a multidomain lifestyle intervention. In the LipiDiDiet trial [13], an effect size of 0.17 (Cohen’s d) was reported for the 2-year change from baseline on the NTB total score following an intervention with Souvenaid. As FINGER-NL combines a multidomain lifestyle intervention with Souvenaid, an effect size (Cohen’s d) of 0.20 (SD = 1) for NTB total score was anticipated for the 2-year change from baseline on the NTB total score in the HI-group compared to the LI-group. With a power of 90%, 2-sided significance level of α = 0.05 and an anticipated drop-out rate of 12.5%, a total of 1,206 subjects (603 per group after randomization) was considered adequate to detect the desired effect size.

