### Statistical analyses

In alignment with other WW-FINGERS studies, we will test for change in the primary and secondary outcome variables, both within-group and between-group using linear mixed models with random effects for intercept (individuals) and slope (time). Time and randomization group will be entered as fixed effects, study site will be included as fixed covariate. Change in the outcome variables will be modelled by including the interaction term between randomization group and time as fixed effect. The intention-to-treat principle will be used. Missing primary and secondary outcome data will be handled through restricted maximum likelihood (REML) estimation of expected scores in the mixed models. Given the size of FINGER-NL, no additional covariates will be included in the primary model, and differences between individuals will be treated as random nuisance parameters in the REML model [48]. For the primary outcome, the level of significance will be set at 0.05 (two-sided). The Benjamini–Hochberg correction will be used to account for multiple comparisons of correlated secondary and exploratory outcomes.

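### The primary model leaves baseline cognition free to differ between arms and adjusts only for site, so it gives up precision that a common baseline mean would recover

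*Protocol article*

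**What the plan says.** The Primary outcome section defines the endpoint: "The primary outcome is the 2-year change from baseline in a global cognitive composite score". Scores are "standardized z-scores using the cohort-wide means and standard deviations (SD) at baseline", then averaged and standardised again, so the composite has a baseline SD of about 1. Under Study design, "Outcome measurements are conducted at baseline, 12 months (Follow-up 1) and 24 months (Follow-up 2) after randomization". Under Randomization and blinding, "Participants were randomized after providing written informed consent and after completing the baseline visit".

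The Statistical analyses section specifies a linear mixed model with a random intercept and a random slope for time. "Time and randomization group will be entered as fixed effects", site is a fixed covariate, and the treatment effect is the group-by-time interaction. Missing outcomes are handled through REML. Citing the size of the trial, the section says that "no additional covariates will be included in the primary model" and that differences between individuals are treated as random. It gives alignment with sister trials in the network as a reason for the approach. It does not state a common baseline mean or a baseline composite covariate.

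On planning, the Sample size section says "an effect size (Cohen’s d) of 0.20 (SD = 1) for NTB total score was anticipated" for the 2-year change. The other inputs are "With a power of 90%, 2-sided significance level of α = 0.05 and an anticipated drop-out rate of 12.5" per cent, giving 1,206 participants (603 per group).

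**The concern.** Because baseline was measured before allocation, the true difference between arms at that visit is zero. A free group main effect estimates a quantity whose value is already known, and any chance difference it picks up passes into the estimate of change. The random intercept does not prevent this: it describes differences in level between people and does not adjust their change for where they started.

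The rationale from trial size does not meet the point either. A large trial makes serious imbalance unlikely, but the proportional gain in variance from using baseline is the same at any sample size.

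At stake is the width of the primary confidence interval. The planned effect of 0.20 is larger than both effects cited to support it (0.127 and 0.17), and recruitment is closed at 1,210. The analysis is one of the few remaining sources of precision.

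**Working it through.** **1. The plan's own sample size.** Inputs: d = 0.20, SD = 1, two-sided alpha 0.05, power 90%, dropout 12.5%. A two-sample t-test needs 526.3, so 527 per arm. Then 527/0.875 = 602.3, so 603 per arm and 1,206 in total. This matches the stated figure exactly, for an unadjusted two-group comparison of change.

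**2. What the stated model estimates with complete data.** With visits at times 0, 1 and 2 (years), each person's least-squares slope is (Y24 − Y0)/2. The group-by-time effect over two years is therefore the difference between arms in mean (Y24 − Y0). If time is categorical, the month-24 interaction is the same quantity, so the article's silence on the coding of time does not matter here. Site enters as a main effect, constant over visits, and does not adjust the change.

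Generalised least squares for the three-visit model with random intercept and slope, run under seven assumed sets of variance components, gave the same variance for the interaction as for the raw change difference every time (for example 1.0800 and 1.0800).

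**3. Gain from using baseline.** Let the SD be σ at both visits and the baseline to month-24 correlation be rho.
- Change score: variance per person 2σ²(1 − rho).
- Adjusted for baseline: σ²(1 − rho²).
- Ratio: (1 + rho)/2, with no sample size in it.

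In the seven settings (rho about 0.59 to 0.78, SDs not forced equal), a common baseline mean with linear time multiplied the variance by 0.79 to 0.92. ANCOVA on the month-24 score multiplied it by 0.81 to 0.92.

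**4. Power.** Evaluable per arm: 603 × 0.875 = 527.6. Power = Φ(0.20 × √(527.6/2)/s − 1.96) = Φ(3.248/s − 1.96), where s is the relevant SD.
- Reading A: SD = 1 is the SD of the change. Then s = 1 for the stated model (power 90.1%) and s = √((1+rho)/2) after adjustment. At rho 0.7, 3.248/0.922 − 1.96 = 1.563, giving 94.1%.
- Reading B: SD = 1 is the SD of the score. Then s = √(2(1 − rho)) for the stated model and s = √(1 − rho²) after adjustment.

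| rho (assumed) | Variance falls by | SE falls by | Power, reading A | Power, reading B |
|---|---|---|---|---|
| 0.5 | 25% | 13.4% | 90.1% to 96.3% | 90.1% to 96.3% |
| 0.7 | 15% | 7.8% | 90.1% to 94.1% | 98.7% to 99.5% |
| 0.8 | 10% | 5.1% | 90.1% to 92.8% | 99.9% to >99.9% |
| 0.9 | 5% | 2.5% | 90.1% to 91.5% | >99.9% to >99.9% |

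The two readings coincide at rho = 0.5, where 2(1 − rho) = 1.

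**5. Size of a chance imbalance.** With 605 per arm and baseline SD 1, the standard error of the baseline difference is √(2/605) = 0.057. At rho 0.7, an imbalance of one standard error shifts the expected change difference by (1 − 0.7) × 0.057 = 0.017 in the opposite direction, against a target of 0.20.

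**The case against.** The strongest reply is that nothing here is wrong. The estimator is unbiased over randomisation, alpha is preserved, and the sample size was calculated for the same unadjusted comparison of change. Design and analysis agree, the model was chosen on purpose for alignment with sister trials, and a typical chance imbalance moves the estimate little. All of this stands, and it limits the point to efficiency.

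Four stronger readings should be set aside.
- A reader might infer that the model excludes every covariate. It does not: site is included, and only further covariates are ruled out.
- A reader might call the analysis a raw change-score comparison without qualification. That is exact only with complete data. The plan expects 12.5% dropout, and REML then also uses month-12 values and partial records.
- A reader might infer bias from regression to the mean. It acts equally on both arms in expectation and does not bias the randomised contrast; only chance imbalance remains.
- A reader might conclude that the trial is underpowered. The documents do not show this. Under reading B, power already exceeds the target at any rho above 0.5.

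The objection does not justify leaving the precision unused. Trial size does not reduce the proportional gain, and alignment is served by reporting the stated model as well.

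**Conclusion.** The point holds as a loss of precision fixed by explicit wording, not as an error of validity. For rho between 0.5 and 0.9, the stated model's variance could be cut by 25% to 5% and its standard error by 13.4% to 2.5%.

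These figures assume equal SDs at baseline and month 24 and complete data among those evaluable; rho is an assumption because the article gives none. The effect on power depends on what the planning SD refers to. If it is the SD of the change, power goes from about 90% to between 91.5% and 96.3%. If it is the SD of the score, power is already higher at rho above 0.5 and the gain is smaller. The narrower confidence interval is gained under either reading.

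**What to change.** Before unblinding, define the primary analysis as a longitudinal model with:
- one common baseline mean for both arms (no group main effect);
- visit as a category (0, 12 and 24 months);
- group-by-visit terms at 12 and 24 months;
- site as covariate;
- the month-24 contrast as the test.

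Visits should be categorical because, once the baseline is constrained, a linear time term would let the month-12 values pull the month-24 estimate. Adjusting the follow-up scores for the baseline composite is a nearly equivalent alternative. Keep the currently stated model as a named sensitivity analysis for comparison with the sister trials. Other covariates, such as age, sex or education, are not needed for this point, and no calculation here supports them.

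The cost is analysis wording only, since every variable is already collected. The downside is that the harmonised model is no longer primary and a published primary model changes after recruitment has closed. The change should therefore be dated and justified as made while the analysts were blinded. If unblinding has already taken place, the common-baseline model should be reported as a supplementary analysis instead.

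### Site, the stratification factor, enters the primary model only as a time-constant covariate, so the group-by-time test of 2-year change is not adjusted for site differences in change; the cost is a slightly conservative test, not bias.

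*Protocol article*

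**What the plan says.** The Primary outcome section defines the endpoint as a change: "The primary outcome is the 2-year change from baseline in a global cognitive composite score". The Study design section gives three measurement times, at baseline, 12 months and 24 months. Under Randomization and blinding, allocation used "randomly varied permuted blocks of 4 to 6 and an equal 1:1 allocation ratio, stratified by study site".

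The Statistical analyses section specifies "linear mixed models with random effects for intercept (individuals) and slope (time"), with time and randomisation group as fixed effects. Site is handled in one clause: "study site will be included as fixed covariate". The treatment effect is carried by a different term: "Change in the outcome variables will be modelled by including the interaction term between randomization group and time as fixed effect". The same section then states that "no additional covariates will be included in the primary model". The article does not mention a site-by-time or site-by-visit term.

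**The concern.** A trial that stratifies by site and then puts site in the model presumably means the primary test to respect the stratification. As the model is written, it does so only for the level of the score. The tested quantity is a slope difference, and a term that adds the same constant to every visit at a site cannot explain why one site's participants improve more between visits than another's.

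Such differences are conceivable with five sites, each with its own testing staff and possibly its own size of retest gain. The random effects belong to individuals, so any site difference in change goes into the between-person slope variance and residual. Balanced allocation within site means that the true sampling variance of the treatment contrast does not contain this component, yet the estimated standard error does. At stake is a small amount of precision in the primary test, and in secondary tests built on the same model.

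**Working it through.** **Planned size and power.** Inputs from the Sample size section: d = 0.20, SD = 1, two-sided alpha 0.05, power 90%, dropout 12.5%. The t-test calculation gives 526.3, so 527 per arm; 527 / 0.875 = 602.3, so 603 per arm and 1,206 in total, as stated. With 603 × 0.875 = 527.6 completers per arm, the standard error of the contrast is √(2/527.6) = 0.0616. Then 0.20 / 0.0616 = 3.248, and power is Φ(3.248 − 1.960) = 90.1%.

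**Does the site main effect touch the tested contrast?** Write the expected score of person i at site s and time t as a_s + b·t + c·g_i + d·g_i·t. The 24-month change is 2b + 2d·g_i, and a_s has cancelled.

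This was checked by generalised least squares on simulated trials with the stated site sizes (248, 242, 240, 240, 240) and three visits. The variance components were assumed and held fixed: intercept 0.65, slope 0.03, residual 0.35.

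- Complete data, arms balanced within site: the group-by-time estimate differs by about 1e-14 with and without the site main effect, and the SE does not differ (0.0521).
- Complete data, arms deliberately unbalanced within site: 0.2542 (SE 0.0521) with no site term and again with the site main effect; 0.2834 (SE 0.0525) once site-by-time is added.
- 12.5% random dropout, balanced arms: the site main effect moves the estimate by at most 0.005, under 0.1 SE, and the SE by about 3e-6. Adding site-by-time moves the estimate by at most 0.008, against an SE of about 0.055.

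Because the variance components were fixed, these runs show what happens to the estimate but not the precision gain. That gain comes from the estimated variance of change, as follows.

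**Size of the precision loss.** Let the within-site SD of 2-year change be 1 and the between-site SD be s. Without site-by-time the variance of change is estimated as about 1 + s², so the SE is too wide by a factor √(1 + s²). The true two-sided alpha is then 2[1 − Φ(1.960·√(1 + s²))]. The article gives no value for s, so a range is shown.

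| Assumed s | SE factor | True alpha | Power, SD inflated throughout | Power, only the reported SE inflated |
|---|---|---|---|---|
| 0 | 1.000 | 0.0500 | 90.1% | 90.1% |
| 0.05 | 1.001 | 0.0497 | 90.1% | 90.1% |
| 0.10 | 1.005 | 0.0489 | 89.8% | 90.0% |
| 0.20 | 1.020 | 0.0456 | 89.0% | 89.4% |
| 0.30 | 1.044 | 0.0407 | 87.5% | 88.5% |

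The fourth column is Φ(3.248/√(1 + s²) − 1.960), the usual formula with a larger SD. The fifth is Φ(3.248 − 1.960·√(1 + s²)). It keeps the estimate's true spread at its within-site value, which fits balanced stratified allocation better. The fourth column is therefore an upper bound on the loss.

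**If the SD of change is below 1.** Suppose instead that the SD of 1 refers to the score itself and that visits two years apart correlate at ρ. The within-site variance of change is then 2(1 − ρ), and the SE factor is √[1 + s²/(2(1 − ρ))], with s now in baseline-SD units. For assumed ρ of 0.7 and 0.8, s = 0.10 gives √(1 + 0.01/0.6) = 1.008 and √(1 + 0.01/0.4) = 1.012. For s = 0.20 the factors are √(1 + 0.04/0.6) = 1.033 and √(1 + 0.04/0.4) = 1.049.

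**The case against.** The strongest reply is that a condensed article need not list every interaction, that an interaction between two terms already in the model is not plainly an additional covariate, and that the separate analysis plan may contain it. This stands in part: the article does not contradict itself, and the point falls away if the analysis plan already has the term. But the article does state the primary model's fixed effects and which of them carries the treatment effect, and on that statement the stratification factor does not act on the contrast.

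A second reply is that the test remains valid and only marginally conservative, and that the model follows sister trials and is kept simple on purpose. The validity stands. Alignment and simplicity are reasons for the general model form; they are not a real cost of one extra term at about 240 participants per site.

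A reader might infer more than the documents support:

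- That the primary estimate is biased. Permuted blocks within site keep the arms nearly equal at each site, and the unbalanced simulation above does not describe this design.
- That the benefit of stratifying is lost. Balance within site still protects the estimate; only some precision is forgone, and only if sites differ in change.
- That differences between local intervention teams would be removed by the fix. Those teams guide the high-intensity groups, while the low-intensity group receives leaflets through the platform. Team effects are mainly treatment-by-site variation, which a site-by-time term common to both arms removes only in part. Tester and retest differences are the sounder rationale, and the article's trained staff and regular intervision meetings argue against assuming that these are large.

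**Conclusion.** The point holds as a minor matter of efficiency. On the model as written, the site covariate makes no adjustment to the primary contrast with complete data and practically none with the expected dropout. The consequence is a slightly conservative test if sites differ in 2-year change, and nothing if they do not.

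The loss of one percentage point or so of power at the upper end of the main range (s = 0.20) rests on two assumptions that the article cannot settle: the between-site SD of change, and whether the SD of 1 applies to change. Neither the validity of the trial nor its sample size is in question.

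**What to change.** Before unblinding, add site-by-time fixed effects (site-by-visit if visits are coded as categories) to the primary model and to each secondary model that uses all five sites. Outcomes measured only in Groningen are not affected. If the analysis plan already includes the term, confirm this and make the description of the model agree with it.

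The cost is four parameters with linear time, or four per follow-up visit with categorical visits, out of 1,210 participants. The sample size stays as it is.

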## Results

Recruitment started in January 2022 and was completed in May 2023. 2,844 persons expressed their interest in participation and 2,057 underwent telephone screening. A sample of *N* = 1,210 participants were randomized, with equal distribution across study sites (Amsterdam = 248; Maastricht = 242; Wageningen = 240; Groningen = 240; Nijmegen = 240). Baseline measurements were completed in June 2023. The mean age of the randomized participants was 67.6 years (SD: 4.6), 64% were female, 61% high educated, and the mean MOCA score was 26.7 (SD: 2.1). In terms of non-modifiable risk factors, 66% of the participants indicated to have a first-degree family history of dementia and 74% reported subjective memory complaints. Regarding modifiable risk factors, several lifestyle and cardiometabolic risk factors were present at baseline such as physical inactivity (89%), low mental/cognitive activity (50%), low social engagement (39%), hypertension (39%) and high alcohol consumption (39%). The mean body mass index of participants was 28.3 (SD: 4.2) and the total serum cholesterol was 5.4 mmol/L (SD: 1.2). The mean LIBRA score of the sample was 1.3 (SD: 2.7). See Table 3 and Additional file 2 for an overview of the baseline characteristics. The last participant’s, last visit is expected in June 2025.

**Table 3 Tab3:** Baseline characteristics of participants randomized to the trial (*N* = 1,210)

**Variable**	**Participants with information available**	
